### Outcomes

As this is a feasibility study, the primary outcome is recruitment rate with a target to recruit 24 subjects in 11 months for study completion in 18 months. The secondary outcomes will include the following feasibility and clinical outcomes. Feasibility outcomes include refusal rate (number of eligible patients who refuse to participate), retention rate (number of enrolled patients completing the study), and compliance rate (measured by proportion of participants taking at least 80% of their study medications).

Secondary clinical outcomes include LVEF and peak global longitudinal strain (GLS, %), NT-proBNP, NYHA functional class, quality of life score, and clinical events, which will all be measured at 0, 3, 4.5, and 7.5 months. GLS and LVEF will be measured on 2D/3D transthoracic echocardiography. The change in GLS and LVEF with supplementation will be used to detect improvement in cardiac function. Change in NT-proBNP reflects HF severity and prognosis [28]. The change in NYHA functional class will be used to track changes in HF symptoms. For quality of life changes, we selected the Kansas City Cardiomyopathy Questionnaire (KCCQ), which is a self-administered disease-specific questionnaire [29]. It has been shown to be responsive to change in large HF trials [30]. For clinical events, all-cause mortality, HF hospitalizations (hospital stay of ≥ 24 h with confirmed diagnosis of HF using the Boston HF criteria), and HF emergency room (ER) visits (hospital stay < 24 h) will be recorded.

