### Randomization, enrolment, and crossover arrangement

Identical bottles containing either placebo or thiamine will be labeled by the hospital pharmacy using a computer-generated randomization list (allocation concealment). Only the pharmacy and our statistician (LM) have access to the randomization list. All participants, investigators, and the research nurse will be blinded to group assignments.

Consented patients will be randomized to thiamine or placebo, taken orally once daily for 90 days during the first period. The study medication is *thiamine mononitrate*. Capsules in 500 mg dose are produced by the Accurex Health Care Manufacturing Inc. along with identical placebo capsules containing inert filler. Participants will be instructed not to take the following foods or health products within 2 h of taking the study medication: areca (betel), horsetail (equisetum), raw freshwater fish, and raw shellfish. These foods interfere with thiamine absorption.

Patients will be sequentially assigned to the two groups in a typical AB/BA crossover design [23]. The first group (AB) will be given thiamine (treatment A) for 90 days, followed by a 6-week washout period during which no supplements are given. The patients will then be given placebo (treatment B) for 90 days. The second group (BA) will start with placebo, followed by thiamine. Compliance will be tracked by pill counts and thiamine blood test at each clinic visit (0, 3, 4.5, and 7.5 months). Patients may continue with concomitant medical care.

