### Participant timeline

After randomization, patients will attend four study visits: at 0, 3, 4.5, and 7.5 months (Fig. 1). Patients will undergo the following tests at the first visit: (i) 2D/3D transthoracic echocardiogram (determine LVEF and GLS) and (ii) blood sampling for baseline NT-proBNP and erythrocyte TPP (approximately 20 ml of blood). Patients will be instructed not to take any biotin-containing supplements on the day of bloodwork as these can interfere with NT-proBNP assay [33]. Patients will also be asked to complete the KCCQ, followed by an interview with the research nurse for (i) NYHA symptoms, (ii) clinical and medication history, and (iii) physical examination and vital signs. Thereafter, patients will be given a 3-month supply of the study drug to take once a day. Patients will return to the clinic for reassessment and repeat measurements of the above parameters at 3 months. Following a 6-week washout period, patients will attend the 4.5-month visit and the same parameters are measured. The patients will take the alternate drug assignment for another 3 months, followed by a final visit at 7.5 months to measure the parameters. Deaths, hospitalizations, and ER visits will be recorded at each follow-up. The study nurse will look at admission records from local hospitals, including St. Joseph’s Healthcare Hamilton and Hamilton Health Sciences, and ask the patient or caregiver for admissions outside Hamilton. Deaths will be determined from local hospital records or by calling the patient’s emergency contact. If a patient does not attend follow-up visit, contact will be made via phone or caregiver.

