### Statistical analysis

The process of patient selection and flow throughout the study will be summarized using a flow-diagram. Patient demographics and baseline clinical outcome variables will be summarized using descriptive measures. Data will be analyzed based on the intention-to-treat principle, i.e., data for each participant will be analyzed according to allocation irrespective of whether they complied during the treatment period. Missing data will be replaced using multiple imputation techniques [31]. A secondary per-protocol sensitivity analysis will be conducted for comparison. Although our washout period should be sufficient, we will do a pre-test analysis to check for carry-over effects between the groups. The primary feasibility outcome is reached when 24 patients are recruited within 11 months. Other feasibility thresholds are listed in Table 1. Continuous secondary outcome measures will be tested using analysis of covariance (ANCOVA), with outcome measures adjusted for baseline measures and allocation. McNemar’s test will be used for categorical outcomes. The KCCQ will be analyzed descriptively. All tests will be two-sided, meaning that an effect in either direction will be interpreted. The level of significance is set at *α* = 0.05. Baseline characteristics and results will be reported as means (standard deviation), medians (interquartile range), counts (percentages), 95% confidence intervals, and levels of statistical significance where appropriate. Data will be analyzed using SAS 9.4 (SAS Institute, Cary, NC) and reported according to the CONSORT statement [36].

**Table 1 Tab1:** Outcome measures

Outcome measure	Scale	Type	Measure	Method of analysis
Feasibility outcomes				
Enrollment rate per year	Ratio	Continuous	Number of participants enrolled per year	Feasibility threshold: 24 patients per year
Refusal rate	Ratio	Continuous	Number of eligible patients refusing to participate	Feasibility threshold: < 40%
Retention rate	Ratio	Continuous	Number of participants completing study	Feasibility threshold: > 80%
Compliance rate	Ratio	Continuous	Number of participants taking study drug appropriately (≥ 80% study drug)	Feasibility threshold: > 90%
Clinical outcomes				
Imaging changes	Ratio	Continuous	Change in global longitudinal strain on speckle tracking echocardiography and ejection fraction	ANCOVA
Biomarker changes	Ratio	Continuous	Change in NT-proBNP	ANCOVA
Functional changes	Ratio	Categorical	Changes in NYHA class	McNemar’s test

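### The primary recruitment outcome carries two thresholds: 24 patients within 11 months in the text, 24 per year in Table 1

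*Protocol article*

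**What the plan says.** The Outcomes section names one primary outcome, "recruitment rate with a target to recruit 24 subjects in 11 months for study completion in 18 months". It lists the secondary feasibility outcomes as refusal, retention and compliance.

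The Statistical analysis section turns the target into a success rule: "The primary feasibility outcome is reached when 24 patients are recruited within 11 months". The next sentence reads "Other feasibility thresholds are listed in Table 1". Table 1, however, opens with an enrolment row whose entry is "Feasibility threshold: 24 patients per year".

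On follow-up, the Participant timeline section says "After randomization, patients will attend four study visits: at 0, 3, 4.5, and 7.5 months". The section on randomization, enrolment and crossover arrangement gives the same schedule in days and weeks. The first group "will be given thiamine (treatment A) for 90 days, followed by a 6-week washout period during which no supplements are given"; then "The patients will then be given placebo (treatment B) for 90 days". The second group takes the two treatments in the opposite order over the same periods.

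**The concern.** Twenty-four patients in 11 months and 24 patients in a year are different accrual rates, and both are presented as the bar for the same outcome. The Table 1 row cannot be read as a separate secondary measure, because enrolment is not among the secondary feasibility outcomes in the Outcomes section. It is the primary outcome on another time base.

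Recruitment feasibility is the first aim listed in the Background. If accrual falls between the two thresholds, a report that follows Table 1 would call the primary outcome met, and a report that follows the text would call it not met.

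The 18-month completion figure attached to the target also needs checking, since it has to hold the recruitment window and the follow-up of the last patient.

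**Working it through.** **Inputs**
- Text rule: 24 patients in 11 months (Outcomes; Statistical analysis).
- Table rule: 24 patients per year (Table 1, enrolment row).
- Follow-up per patient: 7.5 months (Participant timeline), or 90 days + 6 weeks + 90 days = 90 + 42 + 90 = 222 days (crossover arrangement).
- Stated completion: 18 months (Outcomes).

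**Step 1. Put both rules on one scale.**
- Text rule: 24 / 11 = 2.18 per month; 24 × 12 / 11 = 26.2 per year.
- Table rule: 24 / 12 = 2.0 per month; 24 × 11 / 12 = 22 in 11 months.
- Gap: 26.2 / 24 = 1.09, about 9% in rate, or 2 patients at month 11.

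**Step 2. Find the results on which the rules disagree.**
- Table rule read as a rate at month 11: 22 patients give 22 × 12 / 11 = 24.0 per year and 23 give 25.1 per year. Both meet the table and fail the text.
- Table rule read as a count over 12 months: a 24th patient who enters after month 11 and by month 12 meets the table and fails the text.
- The reverse cannot happen. Any trial that meets the text rule also meets the table rule.

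**Step 3. How often would this matter?** The article gives no accrual model, so Poisson accrual is an assumption here. Because the rules are nested, the probability that they disagree is the difference between the probabilities of meeting each.

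| Assumed true rate | P(at least 24 in 11 months) | P(at least 24 in 12 months) | Disagree |
|---|---|---|---|
| 24 per year | 0.363 | 0.527 | 0.527 − 0.363 = 0.164 |
| 26.2 per year | 0.527 | 0.692 | 0.692 − 0.527 = 0.165 |

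With the table read as a rate at month 11 and a true 24 per year, P(at least 22 in 11 months) = 0.528, and the disagreement is 0.528 − 0.363 = 0.165. The two readings give nearly the same answer, about 16%.

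**Step 4. Try to reproduce the 18 months.** Duration = recruitment window + follow-up of the last patient.
- Nominal months: 11 + 7.5 = 18.5.
- In days, 30-day months: 222 / 30 = 7.4; 11 + 7.4 = 18.4.
- In days, average months: 222 / 30.44 = 7.29; 11 + 7.29 = 18.3.

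None gives 18 if enrolment runs the full 11 months. Working backwards, 18 − 7.5 = 10.5, 18 − 7.4 = 10.6 and 18 − 7.29 = 10.7. Completion by month 18 therefore needs the last patient to enter by about month 10.5 to 10.7. If accrual took the 12 months that Table 1 allows, completion would be at 12 + 7.5 = 19.5 months.

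**The case against.** The best defence is that the primary criterion is not left open. The prose states the 11-month rule in two sections, and only that rule is tied to the primary outcome being reached. The prose then sends the reader to Table 1 for the other thresholds, so the enrolment row could be a loose restatement on a yearly scale. This stands as far as it goes: a reader can tell which rule governs. It does not clear the table cell, which is labelled a feasibility threshold, is not marked as rounded, and gives a lower bar for the same outcome.

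A reader might infer more than the article supports in three ways:
- **That the threshold decides whether the larger trial goes ahead.** No section says so. The article says the results will inform the feasibility and planning of a definitive trial.
- **That the 0.36 alone measures the conflict.** At a true 24 per year the table's own rule is met with probability only 0.53, so the part due to the conflict is the difference of about 0.16.
- **That the trial is unable to finish in 18 months.** The rule asks for 24 patients within 11 months, so recruitment may end sooner, and entry of the last patient by about month 10.5 to 10.7 keeps the 18 months. The excess is at most 0.3 to 0.5 month, which whole-month rounding might explain, though the article does not say that the figure is rounded. No endpoint, analysis or sample size depends on it.

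**Conclusion.** The inconsistency is real and modest. The text requires 24 patients within 11 months (26.2 per year) and Table 1 requires 24 per year (22 in 11 months). Under assumed Poisson accrual near either threshold, the two would give opposite answers about 16% of the time; well away from both thresholds they would rarely differ. The arithmetic of the two rates rests only on the article's own figures; the probabilities rest on the Poisson assumption and on the assumed true rate.

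It would go too far to say that the primary outcome has no defined criterion, since the prose supplies one. The defect is that a threshold in the outcome table contradicts it. Correction is worthwhile because this is the trial's only primary outcome.

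The completion figure is a minor side point: 18.3 to 18.5 months against the stated 18, and only when enrolment uses nearly all of its window.

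**What to change.** Keep the rule that the text states. Change the Table 1 enrolment row to read 24 within 11 months (26.2 per year), so that the Outcomes section, the Statistical analysis section and the table agree. Restate study completion as about 18.5 months.

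The cost is one table cell and one timeline figure. No patients, visits or analyses are added, and the recruitment dates needed to apply the rule will exist in any case.

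Shortening the enrolment window to 10.5 months to protect the 18-month figure is not advised. It would raise the primary criterion to 24 × 12 / 10.5 = 27.4 per year, and the Trial status section puts the start of enrolment in May 2018, before the article's publication in September 2018. That would change the primary criterion after enrolment was due to begin, which is more than a wording correction.

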### Data collection

All outcome data will be recorded on paper case report forms (CRF) and stored online using REDCap electronic data capture tools hosted at Hamilton Health Sciences [31]. Raw data from 2D/3D echocardiogram machines will be recorded directly into the CRF and secondary echocardiogram variables will be calculated from raw data. The NYHA functional class will be determined clinically by an investigator at each visit using the criteria published by the American Heart Association in 1994 [32]. The KCCQ is a self-administered disease-specific questionnaire [29]. Erythrocyte TPP level will be measured by a local hospital laboratory. NT-proBNP will be measured on a point-of-care device by a technician at the Hamilton Health Sciences laboratory.

### Participant timeline

After randomization, patients will attend four study visits: at 0, 3, 4.5, and 7.5 months (Fig. 1). Patients will undergo the following tests at the first visit: (i) 2D/3D transthoracic echocardiogram (determine LVEF and GLS) and (ii) blood sampling for baseline NT-proBNP and erythrocyte TPP (approximately 20 ml of blood). Patients will be instructed not to take any biotin-containing supplements on the day of bloodwork as these can interfere with NT-proBNP assay [33]. Patients will also be asked to complete the KCCQ, followed by an interview with the research nurse for (i) NYHA symptoms, (ii) clinical and medication history, and (iii) physical examination and vital signs. Thereafter, patients will be given a 3-month supply of the study drug to take once a day. Patients will return to the clinic for reassessment and repeat measurements of the above parameters at 3 months. Following a 6-week washout period, patients will attend the 4.5-month visit and the same parameters are measured. The patients will take the alternate drug assignment for another 3 months, followed by a final visit at 7.5 months to measure the parameters. Deaths, hospitalizations, and ER visits will be recorded at each follow-up. The study nurse will look at admission records from local hospitals, including St. Joseph’s Healthcare Hamilton and Hamilton Health Sciences, and ask the patient or caregiver for admissions outside Hamilton. Deaths will be determined from local hospital records or by calling the patient’s emergency contact. If a patient does not attend follow-up visit, contact will be made via phone or caregiver.

**Fig. 1 Fig1:**
[figure not shown]
Study flow and assessment intervals

### Sample size and recruitment

Using a 95% confidence interval and assuming that 40% of eligible participants will consent to participate in the study, we will need to approach 78 participants in order to recruit 24 (12 per arm). This recruitment rate is based on previous experience with other clinical trials conducted at our site with a similar population. Twelve participants per arm are sufficiently large to inform the feasibility outcomes of the trial and to provide sufficient precision around effect estimates and their variances [34, 35]. Our feasibility trial will be used to inform the following: (i) sample size and power calculations, (ii) expected event rate, (iii) flow of participants, and (iv) dropout rates. This study aims to inform a definitive RCT with clinical endpoint of composite of all-cause mortality and HF hospitalizations.

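### The refusal threshold in Table 1 (below 40%) does not fit the recruitment plan's assumption that 40% of eligible patients consent, which implies about 60% refusal

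*Protocol article*

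**What the plan says.** In the Protocol article, Sample size and recruitment starts from a consent rate, "assuming that 40% of eligible participants will consent to participate in the study", and concludes that "we will need to approach 78 participants in order to recruit 24 (12 per arm". The margin is introduced by "Using a 95% confidence interval", without saying whether the interval is one- or two-sided. The source of the 40% is given: "This recruitment rate is based on previous experience with other clinical trials conducted at our site with a similar population".

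The Outcomes section lists refusal among the secondary feasibility outcomes, as "refusal rate (number of eligible patients who refuse to participate". Table 1, under Statistical analysis, gives the same measure ("Number of eligible patients refusing to participate") and the entry "Feasibility threshold: < 40" per cent.

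The primary criterion is separate: "The primary feasibility outcome is reached when 24 patients are recruited within 11 months". The text then refers to Table 1 for the other thresholds. It does not say how they are to be weighed together.

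**The concern.** Consent and refusal are both expressed relative to eligible patients, so one should be roughly the complement of the other. A plan for 40% consent expects about 60% refusal. A limit below 40% refusal asks for more than 60% consent. The gap is 20 percentage points, too wide for chance variation to bridge at these sample sizes.

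The study's first stated aim is to establish whether recruitment to such a trial is feasible, and refusal is the direct measure of willingness to take part. A threshold that is missed almost surely when recruitment goes to plan cannot separate recruitment that went as expected from recruitment that went badly. The final report would have to record a failed feasibility threshold for a result that the investigators had predicted.

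**Working it through.** **Inputs.** Consent 0.40, 24 to recruit and 78 to approach (Sample size and recruitment); refusal limit below 0.40 of eligible patients (Table 1). Assumptions for the calculation: each eligible patient approached either consents or refuses, and patients decide independently.

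**Step 1: reproduce the 78.** Find the smallest n for which the lower confidence limit for consent still yields 24 participants:

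n × [0.40 − z × √(0.40 × 0.60 / n)] ≥ 24.

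With z = 1.645 (one-sided 95%):
- n = 77 gives 23.73, too few;
- n = 78 gives 78 × (0.40 − 1.645 × 0.05547) = 24.08, enough.

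The stated 78 is reproduced exactly. A two-sided limit (z = 1.96) would give 82, and the simple quotient 24/0.40 gives 60. At 60% consent the same one-sided formula gives 50. So 78 was built on 40% consent, and the 40% in that sentence is not a slip for 40% refusal.

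**Step 2: refusal implied by the plan.**
- Expected case: 24/0.40 = 60 approached, 36 refusals, 36/60 = 60%.
- Margin case: all 78 approaches are needed, 54 refusals, 54/78 = 69%.

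Both exceed 40%.

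**Step 3: chance of meeting each criterion if consent is truly 40%** (binomial; X = number consenting).

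| Event | Condition | Probability |
|---|---|---|
| At least 24 recruited from 78 | X ≥ 24, n = 78 | 0.964 |
| Refusal below 40%, 60 approached | X ≥ 37, n = 60 | 0.0006 |
| Refusal below 40%, 78 approached | X ≥ 47, n = 78 | 0.0002 |
| 24 recruited with refusal below 40% | at most 15 refusals, so X ≥ 24 within n = 39 | 0.005 |

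The last row follows from R/(24 + R) < 0.40, which gives R < 16. If true consent were 50%, ten points better than planned, the chance of refusal below 40% with 78 approached would still be only 0.044.

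**Step 4: what would reconcile the figures as they stand.** With 40% consenting and fewer than 40% refusing, more than 100 − 40 − 40 = 20% of eligible patients must do neither.

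**Step 5: check candidate replacements.**
- Limit of exactly 60%, true refusal 60%: met with probability 0.55 (60 approached, X ≥ 24) or 0.47 (78 approached, X ≥ 32).
- Limit of 54/78 = 69%: with 78 approached this is the event X ≥ 24, met with probability 0.964.
- Limit kept below 40%, consent 60%: 24/0.60 = 40 approaches give at least 24 consents with probability only 0.57. The one-sided 95% formula gives 23.76 at n = 49 and 24.30 at n = 50, hence 50.
- With 50 approached, refusal below 40% needs at least 31 consents. Its probability is 0.45 at 60% consent and 0.92 at 70%.

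**The case against.** A planning assumption and a success threshold serve different purposes. A cautious consent rate protects the number approached, while a threshold may state what a definitive trial would need. That is fair in principle. But the article describes the 40% as site experience in a similar population, not as a worst case, and gives no reason for a limit that this experience makes nearly unattainable.

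Not everyone who fails to consent has refused: some may be undecided or never reached. This could soften the result, but it needs more than one eligible patient in five to fall in that group. The article describes no such group, its 78 counts patients approached, and patients unable to consent are excluded as ineligible.

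Three stronger readings are tempting and do not hold:
- A reader might infer that the trial would be declared infeasible, or that its conclusion would contradict itself. Refusal is a secondary feasibility outcome, there is no go/no-go or combining rule, and meeting one criterion while missing another is a mixed result.
- A reader might take 69% as the refusal expected under the plan. It is the edge of the 95% margin; the expected value is 60%.
- A reader might conclude that consent and refusal were simply swapped in Table 1. That is possible, but the article does not show which figure was intended.

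It also stands that treatment comparisons and the primary recruitment criterion are unaffected, and that the raw refusal count remains reportable.

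**Conclusion.** The inconsistency is real and lies between two stated figures, so it is not a detail left to the full protocol or analysis plan. Under the plan's own 40% consent, the primary number is very likely to be obtained from 78 approaches (0.96; this says nothing about the 11-month limit), while the refusal threshold is met with probability below 0.001. This rests on treating eligible non-consenters as refusers, which is how the article reads, and on independent decisions. The 78 itself is sound. The consequence is limited to one secondary feasibility threshold that cannot do its job as written; the documents support nothing wider.

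**What to change.** Reconcile Sample size and recruitment with Table 1 before anyone reviews the refusal data, and state the refusal denominator. Because enrolment was due to begin in May 2018, record the change as a dated amendment with its reason, so that it is not taken for a response to the data. There are two routes:

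- **(a) Keep 40% consent.** Set the refusal limit with the margin that already gives 78: no more than 54/78 = 69%. Do not set it at exactly 60%, which would be missed about half the time under the plan.
- **(b) Keep refusal below 40%.** Restate the consent assumption as above 60%, justify it against the site experience now cited for 40%, and restate the number to approach as about 50 by the same one-sided 95% method, not 40. The assumption should be clearly above 60%: at exactly 60% the threshold would again be met only about half the time.

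The edit is one table entry under (a), or a sentence or two under (b). The cost is a less demanding published threshold under (a), or a less cautious recruitment assumption under (b).
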